### 2.8. Statistical Analysis

The data are collected using electronic case report forms and are password-protected. Only the principal investigator and authorized research personnel may access the data. Range checks on data values will be performed prior to analysis. Continuous variables will be presented as the means ± the standard deviation while categorical data will be presented as frequency and percentage. An analysis of covariance (ANCOVA) will be used to compare the mean HbA1c at week 26 between the three groups. The analysis will be conducted by adjusting for study site and baseline HbA1c of 8.5%. Post-hoc analysis will be performed with the Bonferroni method. The mixed-effect model repeated measures (MMRM) will be used to compare change in HbA1c from the baseline to week 26. For binary outcome variables, such as the rate of achieving the target HbA1c level, a generalized linear mixed model (logistic GLMM) will be used. The fixed effects in the MMRM and GLMM include treatment group indicators, time indicators, and interactions between the treatment group and time. The number of hypoglycemic events will be compared between the groups using the chi-squared or Fisher’s exact test.

Analysis will be performed as both per protocol and intention-to-treat. Unless otherwise specified, analyses will be reported based on the results of the intention-to-treat analysis. For interim analysis, adjustment for multiplicity will be applied. Based on the O’Brien–Fleming test, the significance level will be set at 0.005 and 0.0048 for interim and final analysis, respectively. Analyses will be performed using SAS version 9.3 (SAS Institute Inc., Cary, NC, USA).

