### 2.6. Sample Size Calculations

Based on the previous studies [7,8,26], we assumed a mean difference in the HbA1c level of at least 0.60 between the control and intervention groups and a standard deviation within a group of 0.75 after six months. In a single-factor analysis of variance (ANOVA), it was determined that a sample size of 219 (73 per group) would yield 90% power and a 0.05 significance level. We planned both an interim and a final analysis. Therefore, RB = (2, 0.05, 0.1) = 1.007 was applied as the O’Brien–Fleming test. Finally, a total of 282 subjects (94 per group) are required with a predictive dropout rate of up to 20% to achieve 73 subjects per group. This is an ongoing trial in which 181 participants have been enrolled to date.

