### 2.7. Randomization

Randomization is performed to ensure scientific validity of the clinical trial by maximizing comparability between the groups and to prevent subjective involvement by investigators. An independent statistician having no contact with participants performs the randomization process. Eligible participants who provide written informed consent are randomly assigned to one of the three groups in a 1:1:1 ratio. Random numbers are generated using SAS version 9.3 (SAS Institute Inc., Cary, NC, USA) and sequentially numbered, opaque, sealed envelopes are used for allocation. Stratification is by study site and baseline HbA1c of 8.5% using the stratified permutated block randomization method. As this study is an open-label design, group assignment is known to the participants and HCPs after randomization.

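### Single-step Bonferroni is valid but needlessly conservative for three groups; Holm or a closed test holds the same familywise bound and helps the smaller contrasts

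*Protocol article*

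**What the plan says.** Section 2.8 gives the primary comparison as a three-group test: "An analysis of covariance (ANCOVA) will be used to compare the mean HbA1c at week 26 between the three groups". The pairwise step follows: "Post-hoc analysis will be performed with the Bonferroni method". The section does not give the number of pairs, does not say whether the pairwise tests wait for a significant three-group test, and describes no stepwise or closed procedure.

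On error levels, section 2.8 states that "the significance level will be set at 0.005 and 0.0048 for interim and final analysis, respectively". Section 2.6 sizes the trial on a one-way ANOVA. The effect it assumes is "a mean difference in the HbA1c level of at least 0.60 between the control and intervention groups". For the spread, it takes "a standard deviation within a group of 0.75 after six months". It concludes that "a sample size of 219 (73 per group) would yield 90% power and a 0.05 significance level". It states no difference between Groups 2 and 3. Section 2.7 allocates 1:1:1.

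**The concern.** The ANCOVA can say only that the three means are not all equal. The answers of interest are pairwise: each app group against regular care, and app with against app without professional feedback. Single-step Bonferroni tests every pair at one third of the level (if there are three pairs), whatever the other pairs show.

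With three groups that is stricter than necessary. If any two of the pairwise null hypotheses are true, all three means are equal. The only joint hypothesis above the single pairs is therefore the global null, which the three-group test already covers. Once that test rejects, each pair can be tested at the full level with strong familywise control. Holm reaches nearly the same place without needing the three-group test.

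At stake is power for moderate contrasts. The introduction names the role of healthcare professionals as a gap in earlier work, yet the trial was not sized for Group 2 versus Group 3, and that contrast may well be smaller than 0.60.

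**Working it through.** **Inputs.** 73 per group, SD 0.75 and a design difference of 0.60 (section 2.6); 1:1:1 allocation (section 2.7). Assumptions: three pairs (two also run), two-sided pairwise tests, SD 0.75 used as the residual SD, and a final level of 0.048. The printed 0.0048 is run as well. I use 0.048 as the main case because 0.005 and 0.0048 together do not use an overall 0.05: with an interim look at about half the information, the two-look familywise error under the global null is 0.9%.

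**The plan's own figure.** At 0.05 and 90% power, the ANOVA needs 41 per group for means (0, 0.3, 0.6) and 31 for (0, 0.6, 0.6). So 73 does not follow from the stated inputs; at 73 the three-group test has 99.4% to 99.9% power. That is a separate matter. I take 73 as given.

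**Power of one pair.** The standard error of a difference is 0.75 × √(2/73) = 0.1241. For a true difference Δ, d = Δ/0.1241. Approximate power is Φ(d − z), where z = z(1 − α/2) at the full level and z(1 − α/6) with Bonferroni for three pairs.

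For α = 0.048 these are 1.977 and 2.409. For Δ = 0.30, d = 2.417, so:

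- Bonferroni: Φ(2.417 − 2.409) = 50%
- full level: Φ(2.417 − 1.977) = 67%

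**Simulation** (400,000 trials, pooled variance, α = 0.048, three pairs):

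| Contrast (means of Groups 1, 2, 3) | Bonferroni | Holm | Closed test |
|---|---|---|---|
| 2 v 3, 0.30 (0, 0.5, 0.8) | 50% | 66% | 66% |
| 2 v 3, 0.25 (0, 0.5, 0.75) | 34% | 51% | 51% |
| 2 v 3, 0.20 (0, 0.6, 0.8) | 21% | 35% | 35% |
| 1 v 2, 0.30 (0, 0.3, 0.6) | 50% | 63% | 67% |
| 1 v 2, 0.60 (0, 0.6, 0.6) | 99.2% | 99.5% | 99.7% |

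**Largest possible gain.** Φ(d − z_full) − Φ(d − z_Bonf) peaks at d = (z_full + z_Bonf)/2:

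| Level, number of pairs | Peak at Δ | Gain |
|---|---|---|
| 0.05, three | 0.27 | 17.2 points |
| 0.048, three | 0.27 | 17.1 points |
| 0.0048, three | 0.37 | 13.3 points |
| 0.05, two | 0.26 | 11.2 points |

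At 0.0048, closed-test power for a 0.30 difference goes from 22% to 34%, and for 0.60 from 94.8% to 97.4%.

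**Familywise error at 0.048.**

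| Truth | Three-group test, then Bonferroni | Holm | Closed test |
|---|---|---|---|
| All means equal | 4.0% | 4.2% | 4.8% |
| Only Groups 2 and 3 equal, Group 1 0.60 away | 1.6% | 4.7% | 4.8% |

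With two looks at 0.005 and 0.048, closed-test error is 5.0% to 5.1%, which is 5% within simulation error. Power for a 0.27 difference between Groups 2 and 3 goes from 41% to 58%.

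**Cost of waiting for the three-group test.** At 0.048, requiring it before Bonferroni costs at most about 0.5 points in the configurations run (for example 40.15% against 39.62%). Nearly all the loss comes from dividing the level.

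**The case against.** The strongest reply is that nothing here is wrong. Bonferroni is a standard, valid method with simple simultaneous intervals, and for the contrast that the trial was sized on it costs almost nothing. That stands, and it limits the point to an optional improvement. It does not remove the point: the article fixes a specific procedure, and one that is never less powerful is available at the same bound.

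A reader might infer that the plan pays for multiplicity twice, once through a significant ANCOVA and again through Bonferroni. The article does not support this. The order is implied by calling the pairwise analysis post hoc, but no gate is written, and a gate would cost very little. Holm needs none.

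A reader might also take 17 points as the expected gain. It is a ceiling that needs three pairs, a level near 0.05 and a true difference near 0.27, and none of these three is stated.

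The stated purpose is comparison with regular care, and no Group 2 versus Group 3 objective or effect is set. This also stands. That contrast is the most likely beneficiary but not a declared primary question. The same gain applies to app versus control if the app effect is nearer 0.30.

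Finally, part of the power is bought with error: the bound is unchanged, but actual error rises from about 2% to 4% up to the nominal level.

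**Conclusion.** The point holds as a cheap efficiency gain. Single-step Bonferroni leaves part of the permitted error unused, and Holm or a closed test uses it.

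With 73 per group, SD 0.75, three pairs and a final level of 0.048, power for a 0.30 difference between Groups 2 and 3 rises from about 50% to about 67%. The ceiling runs from 11 to 17 points, depending on the number of pairs and the level. At 0.60 from control the gain is under 1 point at 0.048 and about 2.6 points (closed test) at the printed 0.0048.

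Holm never rejects less than Bonferroni. The closed test never rejects less than Bonferroni placed behind the three-group test. Against ungated Bonferroni it can miss an occasional isolated pair, which is a reason to prefer Holm if no gate is intended.

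The documents do not support reading this as an invalid analysis or as a loss of power for the main comparison.

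**What to change.** Before any comparative data are seen, replace the Bonferroni sentence in section 2.8 with one of these:

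> *Closed test.* If the three-group ANCOVA is significant at the level for that look, each of the three pairwise contrasts is tested at the level for that look.

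> *Holm.* The three pairwise contrasts are tested with Holm's procedure.

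Either way, state the number of pairs. Apply the group-sequential boundary to each pairwise test at each look and, for the closed test, to the three-group test too. Say that a pair not rejected at the interim analysis is tested again at the final one, including when the three-group test has already crossed. Reconcile the printed 0.0048 separately, because any replacement inherits it.

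The cost is a short amendment, with ethics review as section 2.9 requires for changes that may affect conduct. The trial is open-label with 181 of 282 enrolled, so the record should show that the change was made without sight of comparative results.

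The statistical downside is that the intervals matching the tests are per-comparison. If Bonferroni intervals are also shown, label them supplementary. In the 0.30 example about a quarter of significant pairs, (67 − 50)/67, would have a Bonferroni interval that includes zero.

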## Abstract

Controlling type 2 diabetes (T2DM) requires a comprehensive approach including patient education, self-monitoring of blood glucose, individualized behavioral strategies, and frequent contact with healthcare professionals (HCPs). We aimed to compare the efficacy of a personalized lifestyle intervention based on a mobile phone application with regular care in participants with T2DM. This is an ongoing randomized controlled open-label parallel-group trial with a target accrual of 282 participants, of which 181 have been enrolled to date. Participants are randomly assigned to one of three groups: (1) regular care; (2) mobile diabetes management; or (3) mobile diabetes management with HCP feedback. The mobile application is enabled to integrate with both electronic medical records (EMR) and a web-based diabetes management system for HCPs. It can send customized messages based on participants’ responses to lifestyle questionnaires administered at the baseline. The intervention period is 26 weeks followed by observation for 26 weeks. We evaluate the intervention’s features in order to assess its clinical utility and efficacy and compare outcomes with regular care considering relevant clinical factors, such as age, baseline HbA1c, etc. We expect our study to provide new evidence in support of customized mobile application tools for the management of T2DM.

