### 2.2. Intervention

Regardless of the assigned group, all the participants are provided a glucometer (CareSens^®^N IoT, i-SENS, Inc., Seoul, Korea) during the intervention period along with diabetes education including SMBG, diet, and exercise.

The participants in Group 1 (the control group) receive regular care according to the Korean Diabetes Association standards [14]. They are instructed to conduct SMBG four times/day (before the morning meal and 2 h after every meal) and record it. Providers monitor SMBG at every visit and provide regular care (Table 1).

In Groups 2 and 3 (intervention groups), the diabetes management system (iCareD application, Medical Excellence Inc., Seoul, Korea) is used in addition to regular care (Table 1). The instruction for SMBG is the same for all the groups; however, as glucometers transmit data wirelessly through mobile communication technology (long-term evolution), the participants in Groups 2 and 3 can track their SMBG data using the application without manual recording. Further, they can visually track the glycemic status as the glucose level is differentiated by color in the application (Table 2). For example, grey signifies potential hypoglycemia; green indicates a glycemic level within the target range; and red indicates a very high glucose level (Table 2, Figure 3A). The participants are also instructed to upload diet photos through the application. Physical activity is tracked using the Google Fit^®^ mobile application [15]. These data are uploaded to the web-based diabetes management system which is integrated to the EMR system for HCP use. At every visit, providers individualize the intervention based on the data. The participants in Groups 2 and 3 also receive messages about diabetes management through the application three times/week (two standardized messages for diabetes management and lifestyle modification and one customized message depending on the lifestyle questionnaire completed at the baseline). The messages consist of information on general diabetes management, diet, physical activity, and encouragement for self-care (Supplementary Table S1). The messages were developed based on the standard diabetes care and were verified by an independent endocrinologist, nurse, nutritionist, and exercise therapist. The participants in Groups 2 and 3 also receive a monthly report generated from their personal data (glucose, blood pressure, physical activity, and diet) (Figure 3B).

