### 2.4. Primary and Secondary Outcomes

The primary outcome is the change in HbA1c (%) from the baseline to week 26. The secondary outcome is the change in HbA1c (%) and fasting glucose (mg/dL) from week 26 to week 52. Other secondary outcomes include lifestyle changes based on physical activity and diet records; cardiometabolic risk factors (body weight, blood pressure, lipid profile); quality of life using Euro-QOL (EQ-5D-5L); participant satisfaction and adherence; number of unscheduled hospital visits due to hypoglycemia or hyperglycemia; number of hypoglycemia and hyperglycemia episodes; changes in the homeostasis model assessment for insulin resistance and β cell function (HOMA-IR and HOMA-β, respectively); and cost effectiveness.

Exploratory outcomes are the change in diabetes medication; frequency of SMBG; BMI; and albuminuria. Study results will be shared with participants and the larger medical research community through presentation at conferences and publication in peer-reviewed journals.

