Hypoglycemic events, including hospitalization or emergency room visits, are evaluated at every visit. Hypoglycemia is defined as blood glucose level < 70 mg/dL or when participants experience symptoms consistent with hypoglycemia, such as sweating, anxiety, or shakiness, and relief of those symptoms occurs following ingestion of glucose [22,23]. Diabetes management strategies, such as SMBG frequency, physical activity, and diet, are obtained at every visit. Quality of life is assessed using the Korean version of the Euro-QOL (EQ-5D-5L) instrument at the baseline and once every 26 weeks [24,25]. The EQ-5D-5L comprises five dimensions (mobility, self-care, usual activities, pain/discomfort, and anxiety/depression) rated on a scale of five (none, slight, moderate, severe, and extreme). User satisfaction with the mobile application will be surveyed in Groups 2 and 3 at the end of the study. Adherence will be assessed by evaluating the scheduled visits, SMBG frequency, maintenance of physical activity and diet record, and achievement of the HbA1c goal. Any adverse events occurring during the trial will be monitored until resolution and reported as required.

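### Hypoglycemic event counts are assigned a chi-squared or Fisher test with no unit stated: anti-conservative on event totals, and off the stated outcome if applied to participants

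*Protocol article*

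**What the plan says.** Section 2.4 lists, among the secondary outcomes, the "number of hypoglycemia and hyperglycemia episodes". That is a count of episodes, not a count of people affected.

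Section 2.5 sets a threshold that one person can cross repeatedly: "Hypoglycemia is defined as blood glucose level < 70 mg/dL or when participants experience symptoms consistent with hypoglycemia", with relief after glucose in the symptomatic case. It adds: "Hypoglycemic events, including hospitalization or emergency room visits, are evaluated at every visit".

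Section 2.2 says of the control group, "They are instructed to conduct SMBG four times/day", and gives the other two groups the same instruction. The Abstract fixes the duration: "The intervention period is 26 weeks followed by observation for 26 weeks". Section 2.6 plans "with a predictive dropout rate of up to 20" per cent.

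The analysis is in Section 2.8: "The number of hypoglycemic events will be compared between the groups using the chi-squared" or Fisher's exact test. The sentence names no unit of analysis, no exposure term and no allowance for several events in one participant. Just before it, the same section assigns binary outcomes to a logistic mixed model, so the event number is given a test of its own.

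**The concern.** Chi-squared and Fisher tests compare independent units, each classified once. A count of low-glucose episodes is not of that form, because one participant with frequent lows contributes many events that share the same cause.

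If arm totals are put into the test, its reference distribution assumes that the totals vary only as Poisson counts. When people differ in their underlying rate, the totals vary more than that, and a few participants with many readings below the threshold can produce an apparent difference between arms.

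If the test is instead applied to participants with any event, independence is restored but the question changes: someone with one episode and someone with thirty count the same.

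At stake is the reported comparison of hypoglycemia between regular care and the two application arms. Readers will want this comparison beside the HbA1c result, and it could err in either direction.

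**Working it through.** The plan states no hypoglycemia rate, dispersion or power, so there is no figure of its own to reproduce here.

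**Inputs from the documents**
- Three arms, 1:1:1, 94 per arm (Sections 2.6 and 2.7).
- Four scheduled readings a day, so 4 × 7 × 26 = 728 per participant over the intervention period.
- Nominal level 0.05. Section 2.6 gives this for the HbA1c calculation; no separate level is given for hypoglycemia.
- Dropout of up to 20%, not split by arm.

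**Assumed inputs (not in the documents)**
- Mean m of 0.5 to 5 events per participant over 26 weeks.
- Negative binomial counts with variance m(1 + κm), where κ = 0 is Poisson and a larger κ means more variation between people. The variance-to-mean ratio is V = 1 + κm.

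**Step 1. Event totals, equal follow-up.** Each arm total has mean nm and variance nmV. The chi-squared statistic on the three totals divides by nm only, so under the null it behaves as V times a chi-squared variable on 2 degrees of freedom. The true rejection rate is

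P(χ²₂ > 5.991/V) = exp(−2.996/V).

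| V | Example | exp(−2.996/V) |
|---|---|---|
| 1 | Poisson | 0.05 |
| 1.5 | m = 1, κ = 0.5 | 0.14 |
| 2 | m = 1, κ = 1 | 0.22 |
| 9 | m = 4, κ = 2 | 0.72 |

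Simulation agrees: 0.133 at V = 1.5 and 0.220 at V = 2 (m = 1, 1,500 replicates each), 0.71 at V = 9 (4,000 replicates), and 0.043 to 0.055 across the Poisson settings.

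**Step 2. Participants with at least one event, equal follow-up.** In the same simulations (m = 0.5, 1, 2, 5; κ = 0, 0.5, 1, 2) the rejection rate was 0.023 to 0.056. The test is not anti-conservative, but it does not use the number of episodes.

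**Step 3. Unequal follow-up.** Assume dropout of 30%, 15% and 15%, which averages (30 + 15 + 15)/3 = 20%, with dropout times spread evenly over the period and identical Poisson rates in all arms.

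| m | Event totals | Any event | Rate model with offset |
|---|---|---|---|
| 1 | 0.105 | 0.083 | 0.048 |
| 2 | 0.151 | 0.111 | 0.046 |
| 5 | 0.309 | 0.151 | 0.064 |

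With overdispersion added (κ = 1 or 2), event totals reject 0.281 to 0.750 of the time and the any-event test 0.051 to 0.075.

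**Step 4. A suitable model.** A quasi-Poisson rate model with a log follow-up offset rejected 0.044 to 0.062 of the time with equal follow-up, and 0.046 to 0.071 under the unequal dropout of Step 3, overdispersed settings included.

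**The case against.** The strongest reply is that the authors meant participants. Chi-squared and Fisher tests need a contingency table, Section 2.8 summarises categorical data as frequencies and percentages, and a condensed article may say events where it means people with events. On that reading the test holds its size with equal follow-up. This stands, and it limits the charge of an anti-conservative test to the event-total reading. It does not clear the sentence: the secondary outcome is still the number of episodes, and the stated test would not analyse it.

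Second, every inflation figure rests on assumed rates and dispersion, and with Poisson counts and equal follow-up the problem disappears. This also stands. The figures show how the error grows with V; they do not measure an error in this trial. Equal underlying rates across all participants are, however, unlikely for hypoglycemia.

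Third, the dropout allowance is an overall figure. A reader might infer that 20% dropout by itself biases the comparison. The documents do not support that: bias needs dropout that differs between arms, and the 30/15/15 split is only an illustration.

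Fourth, a reader might take this as the trial's main safety outcome. The article lists it among many secondary outcomes and follows adverse events separately.

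Finally, an offset does not remove differences in ascertainment. Glucometer readings reach the application automatically in Groups 2 and 3, while Group 1 records its own. That limit remains after the fix.

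**Conclusion.** The sentence in Section 2.8 is wrong as written, because it assigns a test for classified units to a recurrent count and leaves the unit open. It is a stated method, so it cannot be treated as a detail left to the analysis plan.

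The consequence depends on the reading. On event totals, the nominal 5% test rejects about 14% to 72% of the time for V from 1.5 to 9, under assumed rates and dispersion, and about 5% with Poisson counts and equal follow-up. On participants with any event, the fault is a mismatch with the named outcome, plus sensitivity to follow-up if dropout differs between arms.

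A flat statement that the hypoglycemia p-value is invalid would go too far, since the text does not settle which table is tested. The primary HbA1c analysis is untouched. Severity is moderate.

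**What to change.** In Section 2.8, replace the sentence on hypoglycemic events with two statements.

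1. The number of hypoglycemic episodes per participant is analysed with a negative binomial (or overdispersed Poisson) model containing treatment group, the stratification factors (study site and baseline HbA1c at 8.5%) and log person-time as offset, reported as rate ratios with 95% confidence intervals.
2. The proportion of participants with at least one episode is compared separately with the chi-squared or Fisher's exact test.

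The cost is about two sentences. The model is standard in the software the plan names, and it needs only each participant's episode count and time under observation. The trial was still enrolling when the article was written; the change should be dated before the outcome data are compared by arm.

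### The final-analysis significance level is stated as 0.0048, but the O'Brien–Fleming design in the protocol gives 0.048, ten times larger

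*Protocol article*

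**What the plan says.** Section 2.6 (Sample Size Calculations) sets out the sequential design. The sample size "would yield 90% power and a 0.05 significance level". It continues: "We planned both an interim and a final analysis", and then "RB = (2, 0.05, 0.1) = 1.007 was applied as the O’Brien–Fleming test". The arguments of that factor are two analyses, an overall level of 0.05 and a type II error of 0.1.

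Section 2.8 (Statistical Analysis) then gives the thresholds. Naming the O'Brien–Fleming test as the basis, it states that "the significance level will be set at 0.005 and 0.0048 for interim and final analysis, respectively".

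No other part of the article gives a different final level or explains 0.0048. Neither the sidedness of the test nor the timing of the interim analysis is stated.

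**The concern.** An O'Brien–Fleming boundary is strict at the interim look and close to the full nominal level at the final look. With one interim and an overall level of 0.05, the final level should be only slightly below 0.05. Section 2.8 instead gives a final level that is slightly lower than the interim level, which reverses the shape of the method it names. The digits 48 also suggest that 0.048 was meant.

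This is the only threshold the article gives for the final analysis, and so for the primary outcome, the change in HbA1c to week 26. Applied literally, it would turn a result that is positive under the intended design into a negative one. If it were relaxed tenfold only after the results were known, in an open-label trial, the change would be open to the charge of being data-driven.

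**Working it through.** **Inputs**

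| Input | Value | Source |
|---|---|---|
| Number of analyses | 2 | Section 2.6 |
| Overall level | 0.05 | Section 2.6 |
| Power | 90% | Section 2.6 |
| Inflation factor | 1.007 | Section 2.6 |
| Interim and final levels | 0.005 and 0.0048 | Section 2.8 |
| Difference, SD, n per group | 0.60, 0.75, 73 | Section 2.6 |
| Sidedness | two-sided | assumed |
| Information at interim | one half | assumed; range tried below |

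**Step 1: the boundary.** For two equally spaced looks, the test rejects at the interim if |Z1| ≥ C√2 and at the end if |Z2| ≥ C, where Z1 and Z2 have correlation √0.5. C solves P(|Z1| < C√2, |Z2| < C) = 0.95 under the null hypothesis.

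- C = 1.9774 and C√2 = 2.797.
- Interim level: 2 × [1 − Φ(2.797)] = 0.0052.
- Final level: 2 × [1 − Φ(1.9774)] = 0.0480.

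**Step 2: the protocol's own inflation factor.** The drift of the final Z that gives 90% power with this boundary is 3.253. A fixed-sample test needs 1.960 + 1.282 = 3.242 (3.2415 unrounded). The ratio of information is 3.253² / 3.2415² = 10.582 / 10.507 = 1.0071.

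| Quantity | Stated | Recomputed |
|---|---|---|
| Inflation factor | 1.007 | 1.0071 |
| Interim level | 0.005 | 0.0052 |
| Final level | 0.0048 | 0.0480 |

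Two of the three figures reproduce, so the design has been identified correctly. The third is low by a factor of ten.

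**Step 3: can another reading give 0.0048?**

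| Variant | Interim level | Final level |
|---|---|---|
| Classical boundary, information fraction 0.30 to 0.75 | 0.0003 to 0.020 | 0.044 to 0.050 |
| Lan–DeMets O'Brien–Fleming spending, same fractions | 0.0003 to 0.024 | 0.042 to 0.050 |
| One-sided 0.05 | 0.0088 | 0.0467 |
| One-sided 0.025 | 0.0026 | 0.0240 |
| 0.05 split over 2 comparisons | 0.0015 | 0.0244 |
| 0.05 split over 3 comparisons | 0.0007 | 0.0164 |
| Overall level 0.005 | 0.00007 | 0.0050 |

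No variant starting from 0.05 gives 0.0048. The last row comes near, but it contradicts both the 0.05 of section 2.6 and the stated interim level.

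**Step 4: overall type I error of the stated pair.** The probability of crossing at either look under the null is 0.0088 for 0.005/0.0048 with the interim at half the information. It runs from 0.0093 to 0.0075 as the information fraction goes from 0.3 to 0.8. The pair 0.005/0.048 gives 0.0499.

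**Step 5: power, counting rejection at either look.** For one pairwise comparison the drift is δ / (0.75 × √(2/73)). The figures use a normal approximation.

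| Effect | Drift | With 0.005/0.048 | With 0.005/0.0048 |
|---|---|---|---|
| The effect detected with 90% power | 3.253 | 90% | 68% |
| δ = 0.40 (illustrative, not in the protocol) | 3.22 | 89% | 67% |
| δ = 0.40, both levels divided by 3 | 3.22 | 79% | 54% |
| δ = 0.50 (the reduction cited in the Introduction) | 4.03 | 98% | 89% |
| δ = 0.60 (the planning value) | 4.83 | 99.8% | 98% |

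The top row uses the exact C in place of the rounded 0.005/0.048. At the planning value and the final look only, a two-sample t test has about 97% power at 0.0048 and 94% at 0.0048/3. The overall F test at 0.0048 has 95% (group means 0, 0.3, 0.6) to 99% (0, 0.6, 0.6). Power is this high because a one-way analysis of variance on the stated inputs needs only 31 to 41 per group, against the 73 planned.

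**The case against.** The strongest counter-argument concerns consequence. The error is conservative: it cannot raise the false-positive rate, and at the planned difference of 0.60 the trial keeps at least 94% power even at 0.0048. This stands. The marked loss of power appears only for effects smaller than the planning value, and the 0.40 scenario is an illustration. Smaller effects are still realistic, since the Introduction cites a reduction of 0.5 and describes earlier clinical effects as generally modest.

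Second, two-sided testing and an interim at half the information are inferences. That is true and they are labelled so here, but the conclusion survives every alternative in Step 3.

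Third, this may be a typesetting slip in a condensed article, with the right value in the full protocol or analysis plan. That is possible, and those documents should be checked, but the published number would still need correcting. Because the correct level follows almost mechanically from section 2.6, even a late erratum would have some defence. It is simply far easier to defend before the results are known.

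Fourth, how the Bonferroni comparisons share the level is a detail that an analysis plan may settle. This also stands: the article does not say that they divide 0.05, so there is no misstatement on that point.

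**Conclusion.** The concern holds. The final level of 0.0048 is inconsistent with the O'Brien–Fleming design, the overall level of 0.05 and the inflation factor of 1.007 that the protocol itself states. The value those inputs give is 0.048. Followed literally, the trial would run at an overall level of about 0.009 in place of 0.05, and power for an effect at the design's 90% point would fall to 68%. The exact figures assume two-sided testing and an interim at half the information; the tenfold discrepancy does not depend on them to any material degree. The practical loss is small if the true difference is 0.60 and grows as it shrinks. Because the number decides whether the primary outcome is positive, it must be corrected.

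**What to change.** In section 2.8, replace 0.0048 with 0.048. If the interim falls at half the information, the pair to four decimals is 0.0052 and 0.0480. Check the full protocol and the analysis plan for the same figure, and record the correction with a date before the final analysis, citing the design in section 2.6 as its basis.

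It would help, though it is not needed to correct the error, to state that testing is two-sided, when the interim takes place, and that the Bonferroni comparisons at the final analysis divide 0.048.

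The cost is one corrected number and its review under the amendment procedure in section 2.9. No participants, visits or procedures are affected.
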